**Methods:**

The study will be conducted in one of the six geographic divisions of a state in western India. 540 adolescent students from randomly selected urban and rural schools across five districts of this division will be included after informed assent and parental consent. Students’ heights, weights, school bag weights, and the presence and characteristics of back pain will be recorded with an on-site clinical examination by a pediatric orthopedic surgeon to rule out specific causes. Those with nonspecific back pain will perform SanSKAR: at least 12 Surya Namaskars daily at least five days a week for 16 weeks with screen time exposure of not more than 60 min per day. Post-intervention outcomes (proportion of students with back pain and its severity) will be measured at 8 weeks and 16 weeks.

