**Figure 1 F1:**
[figure not shown]
The twelve Surya Namaskar poses.

SNs have been proven to enhance cardiorespiratory fitness levels, “promote weight management” (27), and be a better alternative to aerobic exercise when compared with endurance training on a stationary bicycle (28). The effect of SNs on the involved muscles using electromyography (29) has shown that SNs improve the mobility of almost all the joints of the body, with “high-to-moderate activation” of all the major truncal and lower limb muscles, concluding that SNs can be safely prescribed for not only the management but also the prevention of mechanical back pain. SNs have been shown to result in psychological benefits such as reduction in stress, anxiety, and depression, as well as improvements in emotional intelligence and quality of life in adults as well as children and adolescents (30–37).

Interventions to reduce screen time in adolescents have involved parental participation through interactive group sessions, informative flyers, posters, reminders, and maintenance of log books (38, 39). Since back pain in children is a complex conglomeration of various physical and psychosocial factors, an ideal intervention would need to be tailored to address both.

There is sufficient evidence in the currently available scientific literature to hypothesize that a structured intervention tailor-made for implementation in the school environment that includes performing Surya Namaskars and limiting screen time exposure with parent and teacher engagement could be beneficial in reducing the prevalence and intensity of non-specific back pain in adolescents. Such an intervention needs to be feasible for execution in the school environment, requiring minimal resources, and garnering student, teacher, and parent engagement so that the shared responsibility makes it more acceptable and practical.

The objectives of this study are to test a novel comprehensive intervention module “SanSKAR” (Screen time reduction and Surya Namaskars for 16 weeks) for reducing the proportion of school-going adolescents aged 10–16 years reporting moderate-to-severe back pain as well as the overall proportion of students with back pain.

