**Figure 2 F2:**
[figure not shown]
Pune division, maharashtra state (area of study marked in the black triangle).

Random numbers will be generated using Microsoft Excel against the lists of urban and rural schools. These numbers will be arranged in ascending order, and the first school from each pool will be approached for permission to conduct the study. If permission is refused, the next school on the list will be approached. Schools will be enrolled till the desired sample size is met. The respective school Principals will be approached for permission to conduct the study. Girls and boys studying in standards 5, 7, and 9 (who are typically between ages 10 and 16 years in Indian schools) will be enrolled as representatives of the adolescent age group if they provide written assent and parental written informed consent. Students younger than 10 years will be excluded.

This is a before-and-after study to be carried out in three phases. Phase I, where the baseline pre-intervention data will be collected; Phase II, where the intervention (SanSKAR) will be carried out on students reporting back pain; and Phase III, where the post-intervention data will be collected at the end of 8 and 16 weeks.

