### Phase II

#### The intervention

SanSKAR (**S**creen time reduction **an**d Surya Namas**kar**s) for students reporting back pain in Phase I.

Screen time reduction: The researcher will counsel class teachers and parents using a PowerPoint presentation and handouts detailing the intervention, including SNs and screen time reduction to not more than 60 min per day across all devices such as mobile phones, computers, laptops, tablets, and television. The counseling will include evidence-based recommendations on age-appropriate screen time exposure (41). This will be reinforced at teacher and parent engagements in weekly or fortnightly (as possible) meetings for repeated and regular advocacy and monitoring. Weekly reminders about limiting screen time exposure will be sent to the parents through the official school communication channel. The parents will be handed out a daily diary to record their child's daily screen time usage. In addition, parents will be urged to enforce a complete restriction on their child's involvement in heavy domestic or farm work (as applicable, depending upon the urban or rural setting).

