### Phase III

Data collection will be done at the end of the 8th and 16th weeks for outcomes of interest such as the proportion of students reporting back pain, the intensity of back pain, and SDQ scores. The frequency and number of SNs performed will be noted as well as daily screen time durations. Associations if any between back pain and the physical and psychosocial factors will be determined using appropriate statistical tests. Differences in the pre- and post-intervention phases will be reported.

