## Data analysis

Data will be entered in Microsoft Excel and then imported to SPSS (version 25) for Windows package (IBM SPSS Statistics for Windows, Version 25.0. Armonk, NY: IBM Corp). The associations between qualitative and quantitative variables will be determined using the chi-square test. Odds ratios will be obtained for each predictor. Multivariate regression analysis will be carried out to determine predictors of outcome variables. Pre- and post-intervention variables of interest will be analyzed by comparing their means using the paired *t*-test or comparing proportions using the McNemar test.

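### Any back pain is tested before and after with McNemar, but treatment goes only to students already in pain and the follow-up denominator is not fixed; among treated students the test is close to uninformative

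*Protocol article*

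**What the plan says.** All from the Protocol article:

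- **Objectives (end of Introduction).** There are two: to reduce the proportion of adolescents "reporting moderate-to-severe back pain as well as the overall proportion of students with back pain".
- **Who is enrolled (Abstract, Methods).** "540 adolescent students from randomly selected urban and rural schools across five districts of this division will be included". Enrolment does not depend on having pain.
- **Who is treated.** The Abstract states: "Those with nonspecific back pain will perform SanSKAR". Methods and analysis describes "Phase II, where the intervention (SanSKAR) will be carried out on students reporting back pain". The intervention section under Phase II says SanSKAR is "for students reporting back pain in Phase I".
- **What is measured afterwards (Phase III).** Data at weeks 8 and 16 cover "outcomes of interest such as the proportion of students reporting back pain", together with pain intensity, SDQ scores, Surya Namaskars performed and daily screen time. The section does not say which students supply these data.
- **Test (Data analysis).** Pre/post variables are compared by paired t-test for means or by "comparing proportions using the McNemar test".
- **Design.** Before-and-after, with no control group described. Back pain at baseline is recorded over a one-month recall.

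**The concern.** McNemar's test sets yes-to-no changes against no-to-yes changes. If the paired analysis of any back pain uses the treated students, every one of them is a yes at baseline because that is how they were selected. The no-to-yes cell is then zero by design, and the null hypothesis of equal proportions is true only if nobody at all stops reporting pain.

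A complaint recorded over one month in adolescents will fluctuate. With no control group, the ordinary recovery side of that turnover would be reported as a significant fall, while the onset side among classmates would go uncounted. The objective is worded as an overall proportion of students, and that quantity needs both sides. The gap also affects data collection: onsets among classmates who are not asked at weeks 8 and 16 cannot be recovered by any later analysis.

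**Working it through.** **1. The plan's own figure first.** Inputs from Methods and analysis: 71.6% moderate-to-severe pain, a 15% reduction, 95% confidence (taken as two-sided alpha 0.05), 90% power, 20% dropout, stated result 270. Reading the reduction as 15 percentage points (71.6% to 56.6%) and assuming independent before and after responses:

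- yes-to-no cell: 0.716 × 0.434 = 0.311
- no-to-yes cell: 0.566 × 0.284 = 0.161
- total discordant pd = 0.471, difference d = 0.15
- n = [(1.960 × √pd + 1.282 × √(pd − d²)) / d]² = [(1.960 × 0.687 + 1.282 × 0.670) / 0.15]² ≈ 216
- 216 / 0.8 = 270, as stated.

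This calculation gives the no-to-yes cell about 16%. The sample size for moderate-to-severe pain is therefore not built on an empty cell.

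**2. Any back pain among treated students.** Let b be the number who stop reporting pain; the no-to-yes cell is c = 0. The exact two-sided p is 2 × 0.5^b. The uncorrected chi-square is b and the continuity-corrected one is (b − 1)²/b, each on 1 degree of freedom.

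| b | exact p | corrected p | uncorrected p |
|---|---|---|---|
| 3 | 0.250 | 0.248 | 0.083 |
| 4 | 0.125 | 0.134 | 0.046 |
| 5 | 0.0625 | 0.074 | 0.025 |
| 6 | 0.031 | 0.041 | 0.014 |

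The threshold is six recoveries for the exact and corrected tests and four for the uncorrected one, however many students are treated.

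**3. How easily six is reached.** The article does not give the number of treated students, so it is varied here. The remission rates are also assumptions. The table shows P(b ≥ 6) for b ~ Binomial(n, r):

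| Treated and re-measured (assumed) | r = 5% | r = 10% |
|---|---|---|
| 100 | 0.38 | 0.94 |
| 150 | 0.77 | 0.998 |
| 216 | 0.96 | >0.999 |

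**4. If all enrolled students are re-measured.** The no-to-yes cell can fill, and the recoveries needed for exact p<0.05 rise with the onsets: 5 onsets need 15 recoveries, 10 need 23, 20 need 36 and 40 need 61. The same test on the same outcome is meaningful or close to empty depending on a denominator that the article does not state.

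**The case against.** **The follow-up population is inferred.** A reader might infer that the plan re-measures only treated students and that the overall proportion will never be estimated. The article does not say so. All 540 are surveyed at baseline, and an objective phrased as an overall proportion fits asking everyone again. This stands, and the point is therefore conditional. The treated-only reading remains the natural one: the data are called post-intervention, the Abstract introduces those outcomes directly after the treated group, and Phase III collects Surya Namaskars performed and daily screen time, which Phase II has parents of treated students record.

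**It is not the main test.** A reader might infer that the study's principal analysis is void. It is not. Moderate-to-severe pain is listed first and carries the sample size. For that outcome, treated students with mild pain at baseline can worsen, so the table is not degenerate. Pain intensity is also untouched by this defect. This stands in full.

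**A negative result is still possible.** It is tempting to say that the any-pain test cannot come out negative. With 216 treated students and 3% remission it is significant with probability 0.63, so it fails to reach significance about 37% of the time. What can be said is that significance is very easy to reach and shows little when reached.

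**An article condenses.** Data analysis is one generic sentence for all pre/post variables, and the denominator for each test may be set out in a fuller document. This has some force. However, the outcome, the treated group and the test are all stated here, and it is their combination that fails. Who is asked at weeks 8 and 16 is a matter of conduct, which an analysis plan cannot repair afterwards.

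**Conclusion.** The concern holds in conditional form. For the second of the two objectives, the article leaves the follow-up denominator open. On its natural reading the before value is 100% by selection, the no-to-yes cell is empty, and six recoveries (exact or continuity-corrected test; four if uncorrected) give p<0.05. At 10% remission from any cause, significance is near certain with 150 or more treated students and has probability 0.94 with 100. At 5% it ranges from 0.38 to 0.96 across 100 to 216 students. Those treated numbers and remission rates are assumptions; the p-value thresholds are not.

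A significant fall would then show little beyond the fact that some students stopped reporting pain, and new pain among classmates would not be counted. The conclusion does not extend to the moderate-to-severe objective or to the sample size, and it would lapse for the whole-cohort comparison if all enrolled students are in fact re-measured.

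**What to change.** 1. In Phase III, state that all enrolled students, including those without pain at baseline, answer the back-pain and VAS items at weeks 8 and 16.
2. In Data analysis, state that the overall proportion with back pain and its McNemar comparison are computed on all enrolled students.
3. Among treated students, do not test any back pain against its fixed 100% baseline. Report the proportion pain-free at weeks 8 and 16 with a 95% confidence interval, and beside it the self-reported new onsets among untreated students.

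**Cost.** A short extra form for classmates who are already enrolled, at follow-up points already planned, and a few sentences of text. New onsets would be self-reported only: classifying them as nonspecific in the way baseline cases are would need the on-site clinical examination, which this change does not include. The whole-cohort change will look smaller because untreated students dilute it, and without a control group it still cannot be attributed to SanSKAR. The change has to be made before follow-up data are collected.

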## Discussion

This study will help in the development of a novel multipronged school-based intervention for school-going adolescents with nonspecific back pain. All attempts will be made to refine the intervention to achieve maximum ease of administration, practicality, and acceptability to students, teachers, and parents. The experiences from this study will help inform future planning, especially from the point of view of turning this into a sustainable intervention across urban and rural schools.
